### Data collection

Data will be collected in an electronic case report form (eCRF) only accessible by authorized personnel through two-step verification (REDCap). At baseline assessment, demographic and tumor data is collected. Cognitive status (Montreal Cognitive Assessment, MoCA, scale); neurological symptoms (Neurologic Assessment in Neuro-Oncology, NANO, scale); quality of life (EORTC QLQ-C30 and QLQ-BN20 questionnaires); steroid dependence; and radiological status (RANO) will be assessed. Patients will be monitored in the outpatient clinic according to Table 1.

### Biological specimens

Blood plasma is collected and stored in a valid Swedish biobank that is affiliated with the neurosurgical department. Specimens are primarily stored for future analysis in ancillary exploratory studies.

### Statistical power of endpoints

The power of the endpoints was calculated using data from our pilot study and a thoroughly reviewed Swedish glioblastoma database. An increase in 12-month overall survival from 67.3 to 87.5% (alpha = 0.05, beta = 0.2, power = 0.8) gives a sample size of 132 (66 + 66). An increase in 24-month overall survival from 19 to 40% gives a sample size of 146 (73 + 73). Increase in 6-month PFS from 71.4 to 87.5% gives a sample size of 196 (98 + 98).

### Handling of missing data

The patients are followed according to clinical routine, and data is documented in the patient charts as well as the eCRF. The amount of missing data is expected to be low. Patients who end participation before completing half of the scheduled trial intervention will be excluded and replaced by new patients. Patients who completed more than half of the prescribed trial intervention during concomitant radiochemotherapy will be counted as included. Included patients will be handled according to the intention-to-treat principle.

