### Randomization

Patients included are allocated to Salovum® or placebo egg yolk powder at a ratio of 1:1. Permuted block randomization with blocks of 4–6 will be used and was compiled with R (https://www.R-project.org). To achieve balance between the centers, each study center has its own assigned block list. No stratification is performed. Each patient is assigned a unique consecutive study number. The study number is linked to a box with the same number that contains sachets of Salovum® or placebo egg yolk powder. Each sachet is also marked with the patient’s study number. The placebo and Salovum® powder as well as the packaging look and taste identical. Both patients and investigators are blinded. If a patient needs unblinding, a separate box containing envelopes marked with the patient study number can be accessed. The contents will reveal to which arm the patient was allocated. The investigator who is including the subject to intervention or placebo is unaware of the allocation, which can only be revealed by opening an opaque envelope marked only with the sequential patient study number. The contents of the envelope reveal the allocation.

The allocation sequence was generated by a statistician who is not involved in inclusion, data collection, or clinical evaluations.

The boxes are packed by the trial administrator.

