#### Dosage and timing of intervention

The Salovum® and placebo powder is pre-packed in sachets of 11 g. The dose will be 11 g three times daily. Therapy will be initiated differently dependent on the recommended treatment regime. The following scenarios are possible:Concomitant (60 Gy/30 fractions or shortened with 40.05 Gy/15 fractions) and adjuvant therapy planned: Salovum® or placebo will be initiated 2 days prior to start of concomitant therapy and administered 3 times daily until 14 days after termination of the concomitant therapy. During adjuvant TMZ cycles, Salovum® will be administered from 2 days before, during, and 2 days after each cycle, a total of 9 days for each cycle.Adjuvant TMZ cycles as monotherapy planned: Salovum® or placebo will be administered 2 days before, during, and 2 days after each cycle, a total of 9 days for each cycle.If TMZ is discontinued due to tumor progression, Salovum is also discontinued.

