#### Protocol adherence and monitoring

Protocol adherence will be monitored by frequent visits in the outpatient clinic during treatment (Table 1). Enrolled patients will have access to a research nurse that is involved in the research group. The investigators will have continuous communication with the study sites as well as frequent site visits. An external independent body (Clinical Studies Sweden, Forum South) will monitor the quality of the study. Participants who are in too poor clinical condition to participate in follow-up visits will be monitored for survival.

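### Randomised patients who stop before half of the intervention are excluded and replaced, so the survival comparison is not intention-to-treat and loses early progressors and deaths

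*Protocol article*

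**What the plan says.** Three consecutive sentences under Handling of missing data define who is analysed:

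- The first removes early stoppers: "Patients who end participation before completing half of the scheduled trial intervention will be excluded and replaced by new patients".
- The second sets the condition for being kept, and ties it to the chemoradiation phase: those past the half-way mark in that phase remain in the trial population.
- The third names the analysis principle, but only for the patients who pass that filter: "Included patients will be handled according to the intention-to-treat principle".

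Three other sections bear on the effect of these rules:

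- Randomization places allocation at inclusion, and so before all exposure: "Patients included are allocated to Salovum® or placebo egg yolk powder at a ratio of 1:1".
- Dosage and timing of intervention links the product to disease course: "If TMZ is discontinued due to tumor progression, Salovum is also discontinued".
- Protocol adherence and monitoring keeps survival follow-up for the sickest patients: "Participants who are in too poor clinical condition to participate in follow-up visits will be monitored for survival".

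No section restores an analysis of all randomised patients.

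**The concern.** Membership of the analysis set depends on exposure after randomisation. That is a modified per-protocol set, whatever it is called. In this disease the main reasons for stopping early are likely to include progression, deterioration and death, and none of these is exempted. They are also the events counted by the primary endpoint (12-month survival) and by the interim criterion (6-month progression-free survival).

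Three things are at stake:

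- Survival rates in both arms are overstated if those removed have a worse prognosis.
- The randomised comparison is lost if early stopping differs by arm. The bias can go either way. If Salovum prevents early progression, more poor-prognosis patients are dropped from placebo and the benefit is understated. If more such patients stop on Salovum, a benefit can be manufactured.
- The same rule decides who counts among the 80 interim patients, and so affects the decision to continue.

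The first two sentences also set different thresholds. If that is resolved only after data accrue, the choice of analysis set stays open.

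**Working it through.** **1. The plan's own sample size.** Inputs from Statistical power of endpoints: 67.3% vs 87.5%, alpha 0.05 (taken as two-sided), power 0.80. With the pooled two-proportion formula,

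n per arm = [1.960·√(2·0.774·0.226) + 0.842·√(0.673·0.327 + 0.875·0.125)]² / 0.202² = 66.1.

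This is 66 rounded to nearest (the stated 132) or 67 rounded up (134). The 24-month figure (146) and the 6-month PFS figure (196) reproduce exactly. The sample sizes are not in dispute.

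**2. The two thresholds.** Product in the concomitant part is "initiated 2 days prior to start of concomitant therapy and administered 3 times daily until 14 days after termination of the concomitant therapy". In the adjuvant part it is "2 days before, during, and 2 days after each cycle, a total of 9 days for each cycle", with six cycles under Standard therapy.

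- Standard regimen: 2 + 40 + 14 = 56 days (58 if the six weeks are counted as 42 days), plus 6 × 9 = 54 days. The total is 110 (112).
- Half of the whole schedule: day 55 (56). Half of the concomitant part: day 28 (29).
- A patient who stops on day 40 has taken 40/110 = 36% of the whole schedule, which is excluded under the first sentence. The same patient has taken 40/56 = 71% of the concomitant part (69% on the 58-day count), which is included under the second.
- Temozolomide monotherapy: there is no concomitant part, so the second sentence cannot be met. Under the first, half is 27 of 54 days, or three 28-day cycles. That leaves roughly three months in which progression or death can lead to exclusion.

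**3. Effect on the analysed survival rate.** Let e be the share excluded and s their 12-month survival. Neither is in the article, so both are assumptions. With a true rate of 0.673 in both arms,

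analysed rate = (0.673 − e·s)/(1 − e).

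For e = 0.10 and s = 0.20: (0.673 − 0.020)/0.90 = 72.6%. For e = 0.05: (0.673 − 0.010)/0.95 = 69.8%.

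**4. Type I error at 150 per arm.** Two-sided two-proportion z-test, no true effect:

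P(reject) = Φ[(d − 1.96·SE₀)/SE₁] + Φ[(−d − 1.96·SE₀)/SE₁],

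where d is the difference in analysed rates, SE₀ the pooled standard error and SE₁ the unpooled one. For 10% vs 5% excluded with s = 0.20: d = 0.0277 and SE₀ ≈ SE₁ ≈ 0.0523, giving 0.082.

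| Excluded, arm A vs arm B | Survival of excluded | Analysed rates | False difference | Type I error |
|---|---|---|---|---|
| 10% vs 10% | 20% | 72.6% vs 72.6% | 0 | 5.0% |
| 10% vs 5% | 20% | 72.6% vs 69.8% | 2.8 points | 8% |
| 20% vs 10% | 20% | 79.1% vs 72.6% | 6.6 points | 26% |
| 5% vs 2% | 0% | 70.8% vs 68.7% | 2.2 points | 7% |
| 10% vs 5% | 0% | 74.8% vs 70.8% | 3.9 points | 12% |

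The false advantage goes to the arm that loses more patients. The rows with 0% survival are a worst case. The 20% vs 10% row is extreme: it places 0.20 × 0.80 = 16 of the 32.7 points of 12-month mortality among early stoppers in one arm.

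**5. Power if everyone is kept.** Assume 5%, 10% or 15% of the Salovum arm stop early and have control survival of 67.3%. The Salovum rate becomes 0.875 − e·0.202 = 86.5%, 85.5% or 84.5%. The total N for 80% power becomes 150, 170 or 194. Power at 150 per arm is 0.98, 0.96 or 0.94, against 0.99 without dilution.

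**The case against.** The rule is triggered when a patient ends participation, a term the article does not define. It might mean withdrawal only. Stopping product is not the same thing, since patients too ill for visits are still monitored for survival. This does not rescue the rule. The next sentence makes being counted as included depend on completed exposure, so an early death or an early stop for progression still falls outside. Removing and replacing randomised patients who withdraw would also depart from intention-to-treat.

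The second sentence could be read as spelling out the first for chemoradiation patients, leaving the first for monotherapy. That is possible, but the text does not say so, and read literally the thresholds differ.

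The remaining points limit the size, and they stand:

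- In the standard regimen the window is only about the first four to eight weeks of product.
- Progression is defined conservatively, by conference consensus and a change of treatment, so few progressors may fall in that window.
- Blinding and a matched placebo make similar stopping in the two arms more likely, and equal stopping leaves the null test near 5%.
- Patients who stop for tolerability need not have a poor prognosis.
- Neither the stopping rates nor the survival of stoppers can be taken from the article.

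**Conclusion.** The concern holds and must be fixed. That the analysis set is selected after randomisation and mislabelled as intention-to-treat follows directly from the text and needs no assumption. That the rule removes early progressors and deaths is an inference, but a sound one, because product is tied to progression and neither event is exempted.

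The size is uncertain. With modest exclusion that differs by arm (5% vs 2%, or 10% vs 5%), type I error is roughly 7% to 12% under the assumptions shown. With equal exclusion it stays at 5%, and only the reported survival rates are too high. If very few patients are affected, the rule gains nothing and can simply be removed.

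**What to change.** - Delete the exclusion and replacement rule. For 12- and 24-month survival and for the interim 6-month PFS, analyse every randomised patient in the allocated arm.
- Count the 80 interim patients and the 300 total as randomised patients.
- State that stopping product does not end follow-up. Ask patients who withdraw from the intervention for permission to keep recording survival, and say how those who refuse are handled.
- Keep completion of at least half as a supportive per-protocol set, with one threshold that also works for the shortened regimen and for temozolomide monotherapy.
- Make the change before the interim data are unblinded, and restore any patients already excluded.

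The cost is small. It needs amended wording and survival status for early stoppers. Survival monitoring is already promised for those too ill to attend, and chart documentation is routine. Only patients who withdraw need a new provision. Some dilution by non-adherers is possible, but power stays at 0.94 or more in the scenarios above, and 300 is well over the 132 stated for the primary endpoint.

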### Adverse events

Salovum® is a commercially available product and can be bought in pharmacies in Sweden without a prescription. As it has been available for many years and no toxicities have been reported, no serious adverse events are expected but adverse events will be monitored according to clinical routine and graded according to CTCAE version 5.0. If TMZ is discontinued because of toxicity, Salovum® or placebo will also be paused until TMZ can be reinstated.

### Interim analysis

A Data and Safety Monitoring Committee, consisting of at least one independent statistician and two independent clinicians with knowledge in the field, will perform an interim analysis after the 80th patient has been followed for 6 months. The DMC will assess the outcome based on 6-month PFS. If 6-month PFS differs more than 15% between the groups, the groups are unblinded. If placebo was superior, the study is terminated because of futility. If Salovum® is the superior group, the ethical permit will be amended to include 220 additional patients and continue to phase III. If 6-month PFS differs less than 15% between the groups, the groups are kept blinded and the ethical permit will be amended to include 220 additional patients and continue to phase III.

The 15% cutoff is based on data from the pilot study and our retrospective database. An increase in PFS from 71.4 to 87.5% (controls vs pilot group) is a difference of 18.4% or 16.1 percentage units.

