Antisecretory factor (AF) is an endogenous and essential protein with proposed antisecretory and anti-inflammatory properties [8]. There are currently two approved methods of increasing antisecretory factor levels in humans and animals: SPC-flakes (specially processed cereals) and Salovum®. SPC-flakes consist of oats subjected to malting, a hydrothermal treatment process. Consuming SPC-flakes stimulates endogenous production of AF [9]. Salovum® is a freeze-dried egg yolk powder based on eggs from hens fed with SPC-flakes and contains large amounts of AF [10]. Salovum® and SPC-flakes are classified as medical food by the European Union and can be bought without a prescription in pharmacies in Sweden. Salovum® has been used in clinical trials and case series for a variety of conditions, including diarrheal diseases [11–13], inflammatory bowel disease [9, 14, 15], Ménière’s disease [16–20], and traumatic brain injury [21, 22]. No adverse effects have been reported, even at high doses [13, 15, 23].

AF has been shown to reduce the elevated IFP in experimental models of solid tumors [24]. Ilkhanizadeh et al. demonstrated that exogenous administration of AF reduced IFP levels, increased drug uptake in the tumor, and inhibited tumor growth in glioblastoma-xenografted mice [25]. They also showed that SPC-flakes combined with TMZ successfully prevented tumor growth and increased overall survival at 120 days from 30 to 100% compared to TMZ monotherapy [25]. Our own results show that intratumoral delivery of an active AF peptide, AF-16, boosts the effect of intratumoral chemotherapy and immune reactivity in an experimental glioma model [26].

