### Trial population

Up to 300 patients with newly diagnosed glioblastoma will be enrolled. Patients with newly diagnosed glioblastoma who are discussed in the hospitals’ multidisciplinary treatment conference will be screened for inclusion. Eligible patients are informed and asked to participate prior to starting TMZ therapy, and consent is obtained by one of the investigators or the research nurses. The informed consent form includes use of participant data and biological specimens in ancillary studies. After 80 patients are included in this phase II-III trial, a formal interim analysis will be performed. The interim analysis will guide the investigators to either abandon or proceed to phase III, where an additional 220 patients will be included. If the interim implies that we proceed to phase III, an amendment to the ethical permit will be filed, see Ethics section.

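### The interim rule unblinds the groups, without saying to whom, when 6-month PFS differs by more than 15%, and if Salovum leads it then continues the placebo-controlled trial

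*Protocol article*

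**What the plan says.** The Randomization section defines the blind: "Both patients and investigators are blinded".

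The Interim analysis section says that the DSMC "will perform an interim analysis after the 80th patient has been followed for 6 months", using 6-month PFS. Its rule has three branches:

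- **Difference above 15%, placebo ahead.** The groups are unblinded and the study stops.
- **Difference above 15%, Salovum ahead.** The groups are unblinded ("If 6-month PFS differs more than 15% between the groups, the groups are unblinded") and the trial goes on: "If Salovum® is the superior group, the ethical permit will be amended to include 220 additional patients and continue to phase III".
- **Difference below 15%.** The trial also goes on, but "the groups are kept blinded and the ethical permit will be amended to include 220 additional patients and continue to phase III".

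The Trial population section adds that the interim guides the investigators in abandoning or proceeding, and gives the sizes: "Up to 300 patients with newly diagnosed glioblastoma will be enrolled", and on continuation, "proceed to phase III, where an additional 220 patients will be included". The Ethics section caps the present permit at 100 patients and ties the amendment to a positive trend at the interim. The Background says that Salovum "can be bought without a prescription in pharmacies in Sweden".

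**The concern.** The two continuing branches differ in whether the blind survives, and the article gives no reason for lifting it in one of them. Nor does it name who receives the unblinded information. Read plainly, against a definition of the blind that covers patients and investigators, the rule gives investigators a favourable comparative result and the allocations of the first cohort while randomisation against placebo continues.

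Several features of this trial make that knowledge matter:

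- **Crossover.** The active product needs no prescription, so a placebo patient who hears of a PFS lead can buy it. That dilutes the 12-month survival contrast.
- **Withdrawal.** Under Handling of missing data, patients who leave before half of the intervention are excluded and replaced. Withdrawals prompted by the interim result would therefore drop out of the analysed set, where they could bias the comparison by selection.
- **Enrolment.** Investigators who know of the lead may change whom they approach, and patients may change whether they accept.
- **Progression.** It is declared when a multidisciplinary conference changes treatment, a judgement that known allocation can influence.

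**Working it through.** **1. The plan's own figure.** Statistical power of endpoints gives 196 patients (98 + 98) for 6-month PFS of 71.4% versus 87.5%, alpha 0.05, power 0.80. Sidedness is not stated; I assume two-sided.

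n per arm = [z(0.975)·√(2·p̄(1−p̄)) + z(0.80)·√(p1(1−p1) + p2(1−p2))]² / (p2−p1)²

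With p̄ = (0.714 + 0.875)/2 = 0.7945: 2·p̄(1−p̄) = 0.3265, p1(1−p1) + p2(1−p2) = 0.2042 + 0.1094 = 0.3136, and p2−p1 = 0.161. The result is 2.532/0.02592 = 97.7, so 98 per arm and 196 in total. The stated figure is reproduced, so these rates are a fair basis for the next step.

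**2. Scale of the 15% cutoff.** The Interim analysis section gives the planning difference on two scales, 16.1 points and 18.4%, without saying which one the cutoff uses. 0.161/0.875 = 18.4%, so the relative figure has the higher rate as its denominator; relative to control it would be 0.161/0.714 = 22.5%. I therefore compute all three readings.

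**3. How often the unblind-and-continue branch is reached.** Assume 80 patients split 40/40 (allocation is 1:1) and all evaluable at 6 months. Let C and T be the numbers progression-free on placebo and Salovum, independent binomials with n = 40. In percentage points the branch needs (T−C)/40 > 0.15, that is T−C > 6, so at least 7 patients. Exact enumeration over all (C, T):

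| Reading of 15% | 71.4% vs 87.5% | 71.4% in both arms |
|---|---|---|
| Percentage points, T−C ≥ 7 | 0.493 | 0.053 |
| Relative to the higher rate | 0.630 | 0.129 |
| Relative to control | 0.710 | 0.161 |

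On the plan's own assumptions this branch is a main path of the design.

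**4. Share recruited afterwards.** 220/300 = 73.3% if recruitment stands at 80 when the result is known. No pause after the 80th inclusion is stated, so enrolment could reach the permit cap of 100 first: 200/300 = 66.7%. Hence 67% to 73%.

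**5. State of the first cohort at the interim.** The standard course described in the article is 6 weeks of radiochemotherapy, a 4-week break and six 28-day cycles: 6 + 4 + 24 = 34 weeks, about 8 months. The interim comes once the 80th patient has 6 months of follow-up. The most recently enrolled patients may therefore still be on study product and short of the 12-month primary endpoint when their allocation becomes known.

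**6. What is not exposed.** Under Randomization, each later patient has a new study number, a numbered box and look-alike sachets. Decoding the first cohort does not reveal those allocations. The possible exception is a block still open, which is minor: blocks hold 4 to 6 patients, and those open at patient 80 may have been filled by the time of the interim.

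**The case against.** The strongest reply is that the sentence describes only the committee's own work. The DSMC is the actor in that paragraph, and the branch in which placebo is superior cannot be applied until coded arms are identified. On this reading the DSMC compares coded groups, decodes them if the gap is large, and otherwise leaves them coded. The article also condenses a longer protocol, and access to interim data is often set there or in a charter. The outward action in the two continuing branches, a permit amendment for 220 more patients, is worded alike.

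This stands in part. A committee-only meaning is possible and cannot be excluded. But the article states no such limit, the contrast with a branch that keeps the blind points the other way, and the interim is said to guide the investigators. The rule is also public. If it becomes known which branch applied, and the trial is continuing after unblinding, anyone can infer that Salovum led by more than 15%. The defect is a rule stated loosely, so it is more than a detail left to another document.

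A reader might infer that the double blind ends for about three quarters of the patients. The documents do not support that. What later patients and their investigators could lose is ignorance of the interim result; their own allocations remain concealed.

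Two further limits stand. Twelve-month survival is objective, and PFS is exploratory at the final analysis, so bias in the primary endpoint would have to act through crossover, withdrawal or later care. Over-the-counter access also exists throughout the trial, so the interim result would add a motive for crossover and not create the route.

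**Conclusion.** The concern holds in this form: as written, the rule permits release of a favourable interim comparison, and of the first cohort's allocations, to people who go on treating, assessing and recruiting in a placebo-controlled trial. At the planning rates the branch is reached 49% of the time with the cutoff in percentage points and 63% to 71% with a relative cutoff. With no true difference at 71.4% the figures are 5% and 13% to 16%. Between 67% and 73% of the patients would be recruited afterwards.

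These figures assume 40 evaluable patients per arm and recruitment of between 80 and 100 when the result is known. They measure how often the branch occurs. The size of any resulting bias in 12-month survival depends on crossover and withdrawal rates that the article does not give, so I do not quantify it. That the unblinding reaches beyond the DSMC is the plain reading, but it remains an inference. The wording must be fixed before the interim, because disclosure cannot be undone and the exposure arises in the scenario the trial hopes to see.

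**What to change.** In the Interim analysis section, replace the statement that the groups are unblinded with wording to this effect:

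- Any decoding of the arms is for the DSMC only.
- The DSMC returns only a recommendation to continue or to stop.
- No comparative result and no arm identity goes to investigators, sponsor staff, sites or patients while the trial continues.
- The ethics amendment is worded identically in both continuing branches, saying only that the DSMC recommends continuation. The Ethics section, which now ties the amendment to a positive trend, should be brought into line.

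The DSMC's instructions should carry the same text. While editing the rule, state whether 15% is in percentage points or relative, and if relative, to which rate.

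The cost is a wording change before the interim, with no added patients or procedures. The downside is that the investigators give up early sight of the interim result.

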## Methods

### Trial design

This is a national investigator sponsored, prospective, multicenter, double-blinded, randomized, placebo controlled, phase II-III clinical trial with two parallel groups to assess superiority of Salovum® as add-on to standard treatment in glioblastoma. Allocation ratio is 1:1. Recruitment began in January 2024. Main study center is Skåne University Hospital, Lund, Sweden. Secondary study center is Linköping University Hospital, Linköping, Sweden.

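### The 15% interim cutoff has no stated scale, rests partly on a relative figure taken on the wrong base (18.4% instead of 22.5%), and leaves exactly 15% without an action

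*Protocol article*

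**What the plan says.** The Interim analysis section of the protocol article names the decision variable, "The DMC will assess the outcome based on 6-month PFS", and the timing: the committee "will perform an interim analysis after the 80th patient has been followed for 6 months". Trial design adds "Allocation ratio is 1:1", so about 40 patients per arm are expected.

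The rule has two branches:

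- Above the cutoff: "If 6-month PFS differs more than 15% between the groups, the groups are unblinded". The action then depends on direction. With placebo ahead, the rule is to stop: "If placebo was superior, the study is terminated because of futility". In the opposite direction, the rule is to go on: "If Salovum® is the superior group, the ethical permit will be amended to include 220 additional patients and continue to phase III".
- Below the cutoff: "If 6-month PFS differs less than 15% between the groups", blinding is kept and the trial also goes on to phase III.

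The cutoff is said to come from the pilot study and the retrospective database, and the section closes with "An increase in PFS from 71.4 to 87.5% (controls vs pilot group) is a difference of 18.4% or 16.1 percentage units". The same two rates appear under Statistical power of endpoints, where they give 98 + 98 patients.

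**The concern.** Three things are wrong in the printed rule.

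1. **Scale.** The cutoff is a bare percentage. The justification expresses one difference both as a plain percentage and in percentage units, without saying which of the two the 15% is to be compared with. By the article's own usage, a plain percentage sign means relative. Yet 16.1 points lies just above 15, so a reading in points is as natural.
2. **Figure.** The relative figure does not match the increase that it describes. It is also the only hint of a base for a relative reading, and it points to the higher rate, not to the control rate.
3. **Boundary.** One branch needs more than 15% and the other less than 15%. Equality belongs to neither.

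This is the only quantitative stopping rule that the article gives, and it also triggers unblinding in a double-blind trial with 220 patients still to be recruited. If the scale is settled only once comparative data are visible, the choice can depend on the data.

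**Working it through.** **Inputs.** 6-month PFS of 71.4% (controls) and 87.5% (pilot group), from Interim analysis and Statistical power of endpoints. Interim at 80 patients, 1:1. Assumptions: exactly 40 evaluable patients per arm, and 6-month PFS analysed as a simple proportion.

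**Step 1: the plan's figures.**

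- Absolute difference: 87.5 − 71.4 = 16.1 points. Reproduced.
- Sample size, two-sided 0.05, power 0.8, no continuity correction: n = [1.96·√(2·0.7945·0.2055) + 0.8416·√(0.714·0.286 + 0.875·0.125)]² / 0.161² = 97.7, so 98 per arm. Reproduced.
- Relative increase from the control rate: 16.1/71.4 = 22.5%. The printed 18.4% is not reproduced.
- Other bases: 16.1/87.5 = 18.4%; 16.1 over the midpoint 79.45 = 20.3%; 16.1/28.6 (relative reduction in events) = 56.3%. Only division by the end value gives 18.4%.

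At a control rate of 71.4%, a 15% cutoff relative to control equals 0.15 × 71.4 = 10.7 points, against 15 points on the absolute reading.

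**Step 2: examples with the arms named.**

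| Placebo | Salovum | Points | Relative to higher rate | Relative to lower rate | Consequence |
|---|---|---|---|---|---|
| 30/40 | 25/40 | 12.5 | 5/30 = 16.7% | 5/25 = 20.0% | Points: continue blinded. Relative: unblind and terminate |
| 29/40 | 25/40 | 10.0 | 4/29 = 13.8% | 4/25 = 16.0% | Stops only on the lower-rate base |
| 32/40 | 26/40 | 15.0 | 6/32 = 18.8% | 6/26 = 23.1% | Points: no action defined. Relative: unblind and terminate |
| 28/40 | 33/40 | 12.5 | 5/33 = 15.2% | 5/28 = 17.9% | Continues on every reading; only unblinding differs |

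**Step 3: probabilities.** Let x (placebo) and y (Salovum) be the numbers progression-free at 6 months, independent binomials with n = 40. The cutoff is crossed if |x − y|/40 > 0.15 (points), |x − y|/max(x, y) > 0.15 (higher rate) or |x − y|/min(x, y) > 0.15 (lower rate). The trial stops if the cutoff is crossed and x > y. Exact enumeration gives:

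| True rates, placebo / Salovum | Quantity | Points | Higher rate | Lower rate |
|---|---|---|---|---|
| 71.4% / 71.4% | Stop | 5.35% | 12.91% | 16.15% |
| 71.4% / 71.4% | Unblind, either direction | 10.7% | 25.8% | 32.3% |
| 71.4% / 87.5% | Stop | 0.01% | 0.05% | 0.10% |
| 71.4% / 87.5% | Unblind, either direction | 49% | 63% | 71% |
| 71.4% / 60% (assumed) | Stop | 32% | 52% | 59% |

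When placebo leads, the higher rate is the placebo rate. With equal rates of 71.4%, the points reading and the relative-to-placebo reading disagree on stopping in 7.6% of trials (12.91 − 5.35).

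**Step 4: the tie.** A difference of 6 of 40 is exactly 15.0 points. Its probability is 6.6% with both rates at 71.4% (3.3% with placebo ahead) and 11.2% at 71.4% against 87.5% (0.02% with placebo ahead).

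**The case against.** The strongest reply is that little hangs on this.

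- **Direction.** A reader might infer that the ambiguity can reverse the trial's fate whichever arm leads. The text does not support that: when Salovum leads, both branches continue to phase III. Under the planning effect the stop probability is negligible on every reading, so the 49% to 71% spread is almost entirely unblinding followed by continuation. This part of the reply stands, and the point is limited accordingly.
- **Ties.** A reader might take the exact tie for a common outcome with stopping at stake. The tie probabilities need exactly equal arms. Randomization uses blocks of 4–6 in a separate list for each center, so 40/40 is not guaranteed, and unequal arms or Kaplan–Meier estimates make an exact tie rarer. With placebo ahead, the tie is at most 3.3% in the two scenarios without harm. This also stands. The missing action is still a gap, but a small one.
- **The 18.4%.** A reader might infer that the wrong figure undermines the sample size or the cutoff. It enters no calculation: 98 + 98 follows from the two rates, and 16.1, 18.4 and 22.5 all exceed 15. It is a slip of base in a justifying sentence.

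What the reply does not remove is the unstated scale on the placebo-better side and for unblinding. Nor is this detail that an article may leave to a fuller document: the article prints the cutoff, both branches, the actions and the justification, and the rule as printed can be read in more than one way.

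**Conclusion.** The point holds in limited form. The cutoff has no stated scale or base, 18.4% is wrong for an increase from 71.4% to 87.5% (22.5% is right; 16.1 points is right), and exactly 15% has no action.

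The scale can switch the decision between stopping and continuing only when placebo leads. With no true difference at 71.4%, the chance of stopping then varies threefold by reading (16.15/5.35 = 3.0). If Salovum's true rate were 60%, an assumed value, it would range from 32% to 59%. When Salovum leads, only unblinding is affected, but that is material: under the planning effect its probability moves by 22 points (71 − 49).

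The probabilities rest on 40 patients per arm and simple proportions. The scale ambiguity and the wrong base do not depend on either assumption.

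**What to change.** Before the committee sees any comparative data, the sponsor should:

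1. State the scale of the 15% and, if it is relative, the base rate. One workable form is the magnitude of the difference in 6-month PFS in percentage points, applied in either direction, with the existing placebo-better and Salovum-better actions kept. The wording should not use a signed Salovum-minus-placebo difference with everything below 15 in the other branch. Placebo better by 20 points would then be −20, would fall below 15, and the stopping branch would disappear.
2. Make one branch inclusive so that exactly 15 has an action. The choice has a visible effect: with points, 40 per arm and equal rates of 71.4%, putting the tie in the upper branch raises the chance of stopping from 5.35% to 5.35 + 3.29 = 8.64%.
3. Replace 18.4% with 22.5%, or delete the relative figure and keep 16.1 percentage points.

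The cost is a sentence or two in the interim section and the same wording in the committee's instructions. Sample size and data collection do not change.
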